### Recruitment {15}

#### Pharmacy and general practice recruitment

In the Netherlands, pharmacies will be recruited throughout the country. Pharmacies will be provided with an information sheet via email entailing details about the study. When pharmacies express interest in participation in the study, a member of the research team will contact them via telephone and provides them with additional information after which pharmacies can decide if they want to participate in the study. Participating pharmacies will receive a voucher of €25 for every participant they guide during the study. General practices that will be consulted for registry data on participants’ HbA1c and blood pressure levels will not actively be recruited since they are participants’ caregivers and will receive a voucher of €15 for every participant.

In the UK, remuneration of pharmacies and medical practices will be in accordance with nationally agreed UK tariffs for research. Calculations will include remuneration for medical practices to screen and invite eligible patients and provide baseline and follow-up clinical data for participants. The approximate remuneration will be £500 plus support costs provided by the national clinical research network. Community pharmacies will be remunerated for undertaking training and setting up the site for recruitment, consenting patients, collecting data and intervention delivery. The approximate remuneration will be £100 per patient with an estimated 30 participants per pharmacy.

#### Participant recruitment

As previously described, participants will be selected with an in-practice electronic search in the dispensing records of participating pharmacies by pharmacists in the Netherlands and in the prescribing records of participating general practices by a member of the general practice team in the UK. In the Netherlands, potentially eligible participants are provided with an invitation and information brochure via post as send out by pharmacies. In the UK, invitation and information is provided by general practice teams. Potential participants will express their interest by contacting the researchers in the Netherlands and in the UK by contacting the pharmacies. After expressing interest, informed consent is obtained by a member of the research team. Participating participants will receive a voucher of €10 for participation in the Netherlands and £8.50 in the UK to cover out of pocket expenses arising from study-related internet costs.

## Assignment of interventions: allocation

### Sequence generation {16a}

All participants that provide informed consent and that are eligible for the study will be randomised by variable block randomisation, with a blinded block size of 2:4. The randomisation will be stratified per pharmacy, conducted at participant level and will be normalised for age using a group of 35–55 years and 56–75 years. The sequence generation is performed by the data management platform Castor EDC [29].

### Concealment mechanism {16b}

The randomisation sequence is concealed to those who enrol the patients for the study.

### Implementation {16c}

As soon as a member of the research team has indicated in the data management platform Castor EDC that the participant is suitable for the study and that the participant has given informed consent, allocation will be indicated by Castor EDC [29].

## Assignment of interventions: blinding

### Who will be blinded {17a}

Blinding of the research team, pharmacy team, participants and GPs to treatment allocation is not possible due to the nature of the study.

### Procedure for unblinding if needed {17b}

Because the study is not blinded, a procedure for unblinding is not applicable.

## Data collection and management

### Plans for assessment and collections of outcomes {18a}

Both the research team and pharmacy team will be able to log into the data management platform Castor EDC and introduce the data directly into the system. For some quantitative data, the platform performs a range check and prompts if data are out of range. All questionnaires will be sent automatically as electronic forms to the participants and filled in directly into the data management system. If participants indicate not being able to handle the electronic forms, paper questionnaires will be sent and returned by post and answers will be introduced into the data management platform by a member of the research team. This will be done with a single data introduction procedure that is often combined with a prompt to check whether the introduced data are correct.

The Evalan platform will automatically send out the DTSQs and DTSQc questionnaires as electronic forms to participants and will be used to carry out some of the supporting modules (i.e. brief messaging, reminding messaging and smart messaging).

### Plans to promote participant retention and complete follow-up {18b}

Participants will be reminded twice by the data management platform Castor EDC and Evalan platform in case of electronic questionnaires or by a member of the research team in case of paper questionnaires if no reply has been received. In case of electronic questionnaires, this will be followed by a telephone call conducted by a member of the research team.

### Data management {19}

Both contributing countries will have a separate Castor EDC data management and Evalan platform in which all data will be stored except participant identifiable data that will be stored separately due to aspects of confidentiality.

### Confidentiality {27}

Pharmacies will only be able to access the data that they enter and view the information required to deliver the interventions. The research team in each country will have a log in code to view all data of each participant and will be able to enter data resulting from the telephone calls and paper questionnaires. Apart from the email address of the participant that is needed for sending out the questionnaires, participant identifiable data and audiotapes (see also interim analysis {21} and additional analysis {20}) will be stored separately under lock in each country. These will be only accessible by the country-specific research team. During the study, the research team will have limited access to the management system of each country and the anonymised transcriptions of the interviews of each country. After study completion, all research data collected in the UK will be pseudonymised and transferred to the Netherlands, where it will be stored alongside the research data from the Netherlands for 15 years. Participant identifiable information collected in the UK will be stored in the UK for 12 months after the end of the study.

### Plans for collection, laboratory evaluations and storage of biological specimens for genetic or molecular analysis in this trial/future use {33}

Not applicable, because biological specimens will not be collected or stored.

## Statistical methods

### Statistical methods for primary and secondary outcomes {20a}

#### Effectiveness analysis

Descriptive statistics will be used to describe the study population. Missing data will be imputed by multiple imputation. The effect analyses will be performed according to an intention-to-treat principle, and differences in the primary and secondary outcome measures between the intervention and control group will be analysed with multilevel regression analysis. We shall assess whether age, even after normalising randomisation for this variable, is an interaction factor with regard to the outcome of this study. A *p*-value of <0.05 will be considered statistically significant.

#### Cost-effectiveness analysis

The cost-effectiveness analysis will be performed from a societal perspective. Missing data will be imputed by multiple imputation. The imputed datasets will then be pooled using Rubin’s rules. Incremental cost-effectiveness ratios (ICERs) will be calculated by dividing the difference in mean costs between the intervention and control group by the difference in mean effects between the two groups. Bootstrapping with 5000 replications will be used to estimate bias-corrected and accelerated 95% confidence intervals around cost differences. The bootstrapped incremental cost-effect pairs will be plotted on cost-effectiveness planes, illustrating uncertainty surrounding the ICERs. Cost-effectiveness acceptability curves will also be presented to show the probability that the personalised intervention programme is cost-effective in comparison with the control group for a range of different ceiling ratios.

#### Process evaluation

A process evaluation assesses the extent to which the personalised intervention programme has been performed according to the study protocol and gives insight into the barriers and facilitators in the execution of the intervention programme. We shall assess fidelity, dose and reach according to the Medical Research Council (MRC) process evaluation framework of complex interventions [42, 43]. We will also use the Extended Normalisation Process Theory as a theoretical framework, in order to focus on the feasibility of the intervention programme to be normalised in daily practice [44]. We will use a mixed-methods approach incorporating activities recorded by pharmacists into the Castor EDC data management platform, audio recordings of a sample of pharmacist shared decision making consultations and interviews with relevant stakeholders. These interviews will be conducted among a purposive sample of nine stakeholders involved in the personalised intervention programme, namely participants, pharmacists and in the UK, members of the general practice team. Interviews will be conducted during the pilot phase and overall trial. Interview data will be combined with data recorded in the online data management platform.

The fidelity framework will capture whether the pharmacist conducted shared decision making with the participant on supporting modules to use and whether the pharmacist initiated the supporting modules (i.e. clinical medication review, medication schedule, medication dispensing systems and referral to GP) correctly. These data will be captured from the Castor EDC data management platform and stakeholder interviews. Audio recordings of pharmacists’ consultations will further determine the quality of consultation skills and pharmacists’ compliance to consultation delivery. Through qualitative analysis of participant interviews, we will gain the perspective and opinion of participants on the content of the intervention received. We shall assess through the interviews whether participants and pharmacists thought that the right participants were selected for the study.

The Extended Normalisation Process Theory focusses on the effort that stakeholders have to put into an intervention in order for a complex intervention to normalise and consists of four core elements, namely (I) potential, (II) capacity, (III) capability and (IV) contribution [44]. This evaluation will be based on the interviews with pharmacists.

Table 3 provides an overview of the components of the MRC process evaluation framework of complex interventions and the Extended Normalisation Process Theory.

**Table 3 Tab3:** Framework to perform the process analysis with components of the MRC process evaluation framework of complex interventions [42, 43] and the Extended Normalisation Process Theory [44]. ^*^ HCP refers to pharmacists and/or members of the general practice team

Theory	Theme	Description	Source
**The MRC process evaluation framework of complex interventions**	Fidelity	Delivery of intervention as intended Personalised intervention programme delivered	Interviews with participants and HCPs* Audio recordings from the consultations Entries made by the pharmacist in the data management platform Satisfaction phone call and data recorded in the data management platform after 1 month
	Dose delivered	Personalised intervention programme delivered	Interviews with participants and HCPs* Audio recordings from the consultations Satisfaction phone call and data recorded in the data management platform after 1 month
	Dose received	Intervention received and participants engagement with the intervention	Interviews with participants and HCPs* Quantitative data from practices and pharmacies
	Reach		Interviews with participants and HCPs* Quantitative data from practices and pharmacies
	Recruitment/context	Reasons to participate Barriers to participate	Interviews with participants and HCPs*
**Extended Normalisation Process Theory**	Potential	Commitment Assessment of change efficacy	Interviews with HCPs*
	Capability	Experiences with the intervention Workability	
	Capacity	Changes needed in working processes Feasibility of this change	
	Contribution	Distribution of tasks	

### Interim analysis {21b}

An interim process evaluation analysis will be performed after we have included approximately 25 participants per country. The aim of this analysis is to test the logistics, measurements, questionnaires, training of pharmacists and the usability of other study materials. One month after the start of the study and throughout the study, semi-structured interviews will be conducted among a purposive sample of relevant stakeholders, participants and pharmacists, to conduct a process evaluation. We expect to perform nine interviews in each country. Based on the outcomes of the process evaluation, potential adjustments will be made to the study design during the entire study. With regard to effectiveness of the personalised intervention programme, no interim analysis will be performed.

### Methods for additional analyses (e.g. subgroup analyses) {20b}

#### Non-adherence algorithm

Participants will initially be categorised according to the pre-defined set of non-adherence profiles, namely (I) Knowledge and perceptions, (II) Practical problems, (III) Side effects and (IV) Negative mood and beliefs. After conducting the trial, all available data, including the pre-trial data and log-data, will be used to identify additional factors that influence profiling and profiles will be using subgroup discovery algorithms.

### Methods in analysis to handle protocol non-adherence and any statistical methods to handle missing data {20c}

We shall study protocol non-adherence during the process analysis (Table 3) and will impute missing data by multiple imputation.

### Plans to give access to the full protocol, participant-level data and statistical code {31c}

The protocol and statistical codes can be supplied upon reasonable request to the corresponding author. Participant-level data cannot be supplied because no informed consent will be obtained for data sharing.

## Oversight and monitoring

### Composition of the coordinating centre and trial steering committee {5d}

The coordinating study centre is the Department of General Practice, Amsterdam University Medical Centres, location VUmc, the Netherlands. The Trial Management Committee (TMC) consists of members of the Amsterdam University Medical Centres, Oxford University and University of East Anglia and will be responsible for all aspects of the study planning, randomisation, data registration, data management, biostatistics and study monitoring. The coordinating study centre organises the TMC meetings which are held on average once every 2 months. In addition, in the UK an advisory group has been established. This group comprises of six independent members (i.e. a chair, statistician, behavioural scientist and three patient representatives) and three non-independent members from the TMC. They will convene during the internal pilot phase and thereafter at critical time points.

### Composition of the data monitoring committee, its role and reporting structure {21a}

In the Netherlands, the study will be monitored by a monitor from the Clinical Research Bureau, Amsterdam University Medical Centres, the Netherlands. The University of East Anglia (UK sponsor) decided that no data monitoring board was needed due to the fact that the study was deemed to be in the lowest risk category.

### Adverse event reporting and harms {22}

All adverse events spontaneously reported by participants, the pharmacy team, GP’s or observed by the research team will be recorded.

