### Objectives {7}

Therefore, the aim of the ‘ImproviNg Treatment adhErence iN people with diabeteS mEllitus’ (INTENSE) study is to evaluate the effectiveness of a personalised intervention programme aimed at improving adherence to oral antidiabetic and/or antihypertensive medication in people with T2DM. The intervention programme will be tailored to a participant’s specific situation, needs and preferences and will only be offered to people that have been identified as non-adherent. The effectiveness of the intervention will be tested in a randomised controlled trial in community pharmacies in the Netherlands and the United Kingdom (UK).

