### Criteria for discontinuing or modifying allocated interventions {11b}

One month after the personalised intervention programme was initiated, participants in the intervention group will be contacted by telephone by a member of the research team for a semi-structured interview. This interview will focus on the satisfaction participants have with the selected supporting modules. After this telephone call, a member of the research team will be able to moderate the intensity of some of the interventions (e.g. reduce the frequency of brief messaging) or can actively refer to the pharmacist for other adaptations of the programme (e.g. add a medication box).

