#### Secondary outcome measures

The secondary outcome measures of the study are systolic blood pressure, HbA1c level, self-reported medication adherence, attitude and beliefs toward medication, satisfaction with diabetes treatment, health status and medical consumption and productivity cost. An overview of all the assessments is presented in the Standard Protocol Items Recommendations for Interventional Trials (SPIRIT) diagram in Table 2.

**Table 2 Tab2:** SPIRIT diagram (*t*_0_= baseline; *t*_1_=1 month after baseline; *t*_2_=3 months after baseline; *t*_3_=6 months after baseline) [33]. ^*^Satisfaction phone call will only be performed in participants that receive the intervention condition

	Study period						
	Enrolment	Pre-randomisation	Randomisation	Post-randomisation			
**TIME POINT**				t_0_	t_1_	t_2_	t_3_

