## Discussion

This paper describes the background and study design of the INTENSE study, a study to evaluate the (cost-)effectiveness of a personalised intervention programme compared to usual care in people with T2DM that are non-adherent to oral antidiabetic and/or antihypertensive medication. This personalised intervention programme is hypothesised to increase medication adherence by identifying an individual’s barriers to medication adherence and providing intervention modules to overcome these barriers. We hypothesise that improved medication adherence will lead to a decrease in HbA1c levels and systolic blood pressure and as a result decrease the risk of long-term diabetes complications and health care costs and improve health status of people with T2DM.

This complex multidisciplinary study brings about a number of challenges. The first challenge is the use of a telephone-based pill count as the primary outcome of this study, which is not a widely used measure for medication adherence [45–50]. However, there is currently no gold standard available for the measurement of medication adherence and, therefore, researchers should assess which medication adherence measure is most suitable for their study [32]. We selected a telephone-based pill count since it is practical, has low implementation costs [46, 48] and showed high concordance with home-based pill counts that are conducted more extensively in other patient populations [46–48, 50]. Also, we performed a validation of a telephone-based pill count in 34 people with T2DM or cardiovascular disease accounting for a total of 203 pill counts. In this validation study, a high concordance between a telephone-based and home-based pill count was observed with an intraclass correlation coefficient (ICC) of 0.96 (95% CI 0.94–0.97) ([name], [name], [name], [name], [name], [name]: Validation of an announced telephone pill count compared to a home-visit pill count in people with type 2 diabetes or cardiovascular disease, Submitted).

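### Adverse events are captured passively while one arm has more contacts, so recorded harms may be under-counted and a between-arm comparison may reflect contact intensity

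*Protocol article*

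**What the plan says.** The harms section of the protocol article ({22}) is one sentence. It provides for recording "All adverse events spontaneously reported by participants, the pharmacy team" and GPs, together with events that the research team observes. Table 2, presented as the overview of assessments, and Participant time line {13} list no adverse event enquiry.

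Objectives {7} describes a "personalised intervention programme aimed at improving adherence to oral antidiabetic and/or antihypertensive medication in people with T2DM". The Discussion states the expected consequence: "We hypothesise that improved medication adherence will lead to a decrease in HbA1c levels and systolic blood pressure".

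Contacts differ by arm. Intervention description {11a} gives intervention participants a consultation of about 30 minutes with the pharmacist, followed by modules that include medication review. Table 1 adds GP referral for the side-effects profile. Under {11b}, one month into the programme, "participants in the intervention group will be contacted by telephone by a member of the research team for a semi-structured interview", and the caption of Table 2 confirms: "Satisfaction phone call will only be performed in participants that receive the intervention condition". Controls have one baseline appointment with a pharmacy assistant about a website, alongside usual care (Control group). Section {17a} says that the research team, pharmacy team, participants and GPs are all unblinded. On oversight, {21a} reports the UK sponsor's view that "no data monitoring board was needed due to the fact that the study was deemed to be in the lowest risk category".

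**The concern.** Passive capture finds events when someone has occasion to mention or notice them. Here those occasions are part of the allocated treatment. Of the four named sources, the pharmacy team and the research team have extra planned contact with the intervention arm only, and GPs may have it through the referral module. The fourth source, the participants, has more occasions to speak in that arm. All four know the allocation.

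Harm is also foreseeable in principle. The programme is meant to raise the use of glucose- and blood-pressure-lowering drugs, and unwanted effects of greater exposure are the other side of that mechanism. Side effects are already one of the trial's four non-adherence profiles.

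At stake is what the adverse event table can be made to say. An excess in the intervention arm could not be separated from better detection. The absence of an excess would be weak reassurance, because passive capture can hide a real one.

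**Working it through.** The documents state no adverse event rate, capture rate or safety power, so there is no figure to reproduce. The check has two parts.

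**1. Capture method against contact schedule**

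| Source named in {22} | Intervention arm | Control arm |
|---|---|---|
| Pharmacy team | Pharmacist, about 30 min, plus modules ({11a}) | One assistant appointment, plus usual care |
| Research team | Pill counts at baseline and 6 months, plus 1-month call ({11b}, Table 2) | Pill counts at baseline and 6 months |
| GPs | Usual care, plus referral module (Table 1) | Usual care |
| Participants | Speak at all of the above | Speak at fewer contacts |

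Contacts common to both arms during follow-up are the 3- and 6-month questionnaires and the 6-month pill-count call. None is listed as asking about harms.

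**2. What unequal capture could do (illustration, all rates assumed)**

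Recorded risk = true risk × share captured. With equal true risk, the apparent risk ratio is the share captured in the intervention arm divided by the share captured in controls. The true risk cancels.

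- 0.50 / 0.30 = 1.67
- 0.60 / 0.30 = 2.00

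With 300 participants allocated 1:1 there are about 150 per arm, which gives these recorded participants:

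| True risk, both arms | Control, 30% captured | Intervention, 50% captured | Intervention, 60% captured | Full capture, either arm |
|---|---|---|---|---|
| 10% | 150 × 0.10 × 0.30 = 4.5 | 7.5 | 9 | 15 |
| 20% | 150 × 0.20 × 0.30 = 9 | 15 | 18 | 30 |

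The ratio only restates the assumed capture shares. It shows the mechanism and estimates nothing.

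The opposite error is a true excess that is missed. For a simple two-sided 5% comparison of two proportions with n = 150 per arm, ignoring clustering and loss to follow-up, power = Φ{[|p1 − p2|√n − 1.96√(2p̄(1 − p̄))] / √(p1(1 − p1) + p2(1 − p2))}, where each p is true risk × share captured.

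| True risks | Full capture | 50% captured in both arms | 30% captured in both arms |
|---|---|---|---|
| 20% v 40% | 0.97 | 0.68 | 0.44 |
| 10% v 20% | 0.68 | 0.38 | 0.24 |

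Worked cell: recorded risks of 10% and 20% give [0.1 × 12.247 − 1.96 × 0.505] / 0.5 = 0.47, and Φ(0.47) = 0.68.

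**The case against.** The strongest case on the other side has four parts.

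- **No harm comparison is planned.** Harms are not among the primary or secondary outcomes, and {22} promises only recording. This stands: the plan contradicts no stated aim. The point concerns what the records can support if they are tabulated by arm.
- **Other data bear on harm.** HbA1c and systolic pressure from GP records, EQ-5D-5L and iMCQ healthcare use are collected in both arms without relying on spontaneous report. A reader might infer that the adverse event records are the trial's only information on harm, and that is not so. None of these measures is designated as a harm measure, however, and none is described as asking about adverse events.
- **Risk is low.** Insulin users are excluded, the drugs are already prescribed, and the UK sponsor rated the study in its lowest risk category. This may justify having no monitoring board, and nothing here faults that decision. It does not make ascertainment equal between arms.
- **The article is condensed.** The full protocol and the pill-count script are not shown and may contain harm questions. That is possible. But the article states a capture method, and the point addresses that method.

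Two stronger readings about exposure also fail. A reader might infer that participants are known to take less than 80% of their drugs. Eligibility criteria {10} uses a dispensing score (Netherlands) or prescribing score (UK), and the Discussion acknowledges that dispensing records can differ from what is taken. A reader might also picture a very large rise in intake. The only effect size given, in Sample size {14}, is a 20% relative difference in adherence between arms.

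**Conclusion.** The point holds in a limited form. Capture is passive by the article's own statement, occasions for capture depend on allocation, and every reporter is unblinded. Recorded harms may therefore be under-counted, and a between-arm comparison may reflect contact intensity and not true risk.

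The documents do not support the flat statement that harms will be under-counted and cannot be compared, because they give no event or capture rates. The apparent ratio of 1.67-2.00 rests wholly on the assumed 30% against 50-60% capture, with equal true risk. The power figures rest on assumed risks and equal partial capture. Extra contact could inflate the intervention count, and low capture could hide a true excess, so the net direction is open. The primary adherence analysis is not affected.

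**What to change.** Put the same short, fixed set of harm questions to both arms in the 3- and 6-month questionnaires and in the scripted 6-month pill-count call. Suitable topics are low-glucose symptoms, dizziness or falls, new side effects, and unplanned care or admission. Where iMCQ items already cover unplanned care, use those and do not ask twice.

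State that any between-arm harm summary uses these solicited items only. List spontaneous reports, and events found through intervention-only contacts such as the 1-month call, separately and by source.

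The contacts already exist, so the cost is a few items, a minor amendment and more non-serious events to record. Two limits remain. Answers are self-reported under open allocation, so equal asking removes the contact imbalance but not reporting influenced by knowing the arm. Recruitment was already under way when the article was submitted, so participants past a contact would lack the items. The summary should then be restricted by the calendar date of the contact, applied identically in both arms.
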